#### Covariates

In order to control for factors that might influence the association between treatment and the outcome measures, we collect the following additional data:Medication use:Current medication use is reviewed at each assessment. Since dopaminergic agents can have a positive influence on mood in PD patients with depressive symptoms [60], we will control for the total dose of dopaminomimetics, which is converted to a levodopa equivalent daily dose using the conversion rate described by Olde Dubbelink et al. (2013) [61]. Moreover, we will correct for the initiation or change in dosage of antidepressants or sleep medication.Exposure to environmental light:We collect data on the exposure to environmental light using a light sensor (Actiwatch Light®, Cambridge Neurotechnology Ltd., Cambridge UK). Subjects are asked to continuously wear the sensor on the outer layer of their clothing for seven consecutive days. Raw data on light exposure is preprocessed with Actiwatch Activity & Sleep Analysis 5 software, after which total amount of light exposure during the day is calculated using custom-made in-house software.ExpectancyIn a previous study on BLT, a positive correlation between expectations and treatment response was found [62]. In this study, we assess the expectancies of our subjects with the Credibility/Expectancy Questionnaire (CEQ) [63], after installation of the device at home.Compliance:Compliance with treatment is assessed with an occupancy data logger (HOBO® occupancy/light logger) that is attached to the device. The logger detects the time and duration of presence of the participant in front of the device. Treatment session compliance is defined as exposure to the device for at least 70 % of the prescribed duration, i.e. 21 out of 30 min, within the set time frame. Total compliance is calculated as the proportion of sessions that a subject is compliant with therapy. We assess the effects of total compliance on the intervention effect, as well as compliance with morning and evening therapy separately.

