### Intervention

The experimental condition consists of BLT with a Brazil® Lightbox (Lumie, Cambridge, United Kingdom). This BLT device emits white, broad spectrum light. During treatment sessions, subjects are instructed to take place in front of the device at a distance of 30 cm, at which the intensity of the light is 10,000 Lux. To create a credible control condition, neutral density filters (Lee Filters, type 209.03ND, Hampshire, United Kingdom) are installed in the light device, so that the experimental and control device have an identical appearance when switched off. These filters reduce transmission uniformly, giving the light a dim white appearance. Subjects are instructed to position themselves at a distance of 40 cm from the control device, at which the light intensity is approximately 200 Lux. At this light intensity, which is lower than in a dimly lit room, no substantial effect on circadian rhythmicity is expected [46].

Subjects in both conditions follow the treatment at home for a period of three months. Subjects use the device both in the morning and the evening. Treatment duration per session is 30 min, which is sufficient to entrain the SCN at an intensity of 10,000 Lux [20]. Timing of the morning treatment session is based on the score on the MEQ [19, 41].

Since evening BLT should be administered at least 90 min prior to bedtime [20], the evening session takes place 9. Five hours prior to the morning BLT, in order to allow eight hours of nighttime sleep. To increase user convenience and compliance, the device is attached to a timer, so that the device switches on automatically at the times set for treatment.

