### Statistical analysis

#### Sample size calculation

Prior to the start of the study, we calculated the necessary sample size for a sufficient power at the end of treatment (T2) in a mixed models analysis. We aimed to have sufficient sensitivity for a minimal standardized effect size of Cohen’s d = 0.6, with an estimated standard deviation of 1.0 and intra-subject correlation of assessments of *ρ* = 0.6. For a statistical power of 80 % and a two-tailed significance level of *p* < 0.05, 35 subjects per treatment group were required. To correct for a maximum drop-out of 20 %, we would need 7 additional subjects per group, resulting in a total sample size of 84 subjects.

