#### Efficacy analysis

Analyses will be performed on the Modified-Intent-To-Treat population, which consists of all subjects randomized in the trial who received at least one week of light treatment and provided at least one post-baseline assessment of the HDRS. As a sensitivity analysis, we will compare the baseline characteristics to the Intent-to-Treat population, i.e. all subjects who were randomized in the trial. To assess the effect of treatment duration, we will also assess the effects in the Per Protocol-population, i.e. all subjects who completed the three months treatment duration.

Demographics and clinical characteristics of both the BLT and control group at baseline will be presented with percentages or mean scores with standard deviations. Correlations between continuous variables at baseline will be calculated using Pearson’s correlation coefficients.

The effect of the intervention on the change from T0 to T2, and from T0 to T5, in outcome measures will be assessed using a linear mixed-effects model analysis with assessment visit as the lowest level, and patient as highest level. Time of assessment will be handled as a categorical variable. The effect of the intervention on the outcome measures over time will be modeled by an intervention by time interaction with two degrees of freedom. In all analyses, we will correct for baseline values of the outcome variable. In addition, we will assess whether adding the covariates to the regression model leads to a significant change of the regression coefficient of the condition effect of ≥10 %.

No imputation of missing values will be performed, since linear mixed models handle missing data by placing the data in long format, where the available data of each measurement is nested within persons.

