With our study design, we do not compare BLT to ‘pure’ placebo treatment, i.e. an ineffective control treatment. Rather, we compare structuring of the sleep-wake cycle through set treatment times in both conditions, with additional BLT in the experimental condition, and additional dim light in the control condition. In order to be able to assess the effects of BLT only, a future study on the effects of BLT on depression in PD would have two additional treatment arms, where BLT and control light are administered at random times. Moreover, more research is needed on the timing (morning or evening) and duration of BLT, as well as the influence of light intensity. However, we hypothesize that with the design of this study, we will still find a greater improvement on depression, insomnia and biomarkers of circadian rhythmicity in the subjects in our experimental condition as compared to our control subjects, due to the addition of BLT to the imposed sleep-wake structure.

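### Compliance is self-chosen after randomisation, so its planned link to the treatment effect, overall and by session, can reflect selection and should be reported as descriptive only

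*Protocol article*

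**What the plan says.** All references are to the protocol article.

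- **Measurement (Covariates, compliance item).** An occupancy logger is fixed to the lamp: "The logger detects the time and duration of presence of the participant in front of the device". A session counts as compliant if exposure reaches 70% of the prescribed time, 21 of 30 minutes, in the set window. The summary is per patient: "Total compliance is calculated as the proportion of sessions that a subject is compliant with therapy".
- **Planned use (same item).** "We assess the effects of total compliance on the intervention effect, as well as compliance with morning and evening therapy separately".
- **Role in the efficacy model.** Compliance is listed as a covariate, and Efficacy analysis says of that list that "we will assess whether adding the covariates to the regression model leads to a significant change of the regression coefficient" of the condition effect, with a threshold of 10%.
- **Sessions (Intervention).** "Subjects use the device both in the morning and the evening". This holds in both arms, and the evening time is set at a fixed interval before the morning time.
- **Timing (Discussion).** The authors treat it as open: "more research is needed on the timing (morning or evening) and duration of BLT".

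**The concern.** Asking how compliance changes the intervention effect is a causal question about an exposure that nobody randomised. Patients who keep using the lamp may differ in prognosis from those who stop. The protocol article gives reasons to expect this. Participants excludes current psychosis partly because of likely non-compliance, so clinical state is accepted as a driver of lamp use. Covariates cites an earlier light-therapy study in which "a positive correlation between expectations and treatment response was found", and expectancy could plausibly raise both compliance and improvement.

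The control arm removes this selection from a compliance-by-arm term only if selection is the same in both arms. That cannot be assumed. The lamps differ in intensity (10,000 vs about 200 lux), side effects are to be compared between groups, and the Discussion accepts that the dimmer light may reveal the control condition.

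For the sessions there is one randomised contrast and two self-chosen exposures that are likely to be correlated. What is at stake is a dose-response or session-specific message that reflects only who used the lamp, on a question that the authors themselves call open.

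**Working it through.** **The plan's own figure.** No figure is given for the compliance analysis, so only the trial size can be reproduced. For a "minimal standardized effect size of Cohen’s d = 0.6", SD 1.0, two-sided 0.05 and 80% power, a plain two-sample comparison needs 2 × (1.96 + 0.84)² / 0.6² = 43.6 per group. A variance factor of 2(1 − 0.6) = 0.8 gives 34.9, so 35 per group. Adding 7 gives 42 per group, 84 in total. The checks below use 35 or 38 per arm, within the range from 35 evaluable to 42 randomised.

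**Step 1: false dose effect when light does nothing.** Assumptions: outcome SD 1, mean compliance 75% with SD 20 points, 38 per arm, compliance-outcome correlation r_B in the BLT arm and r_C in the control arm. The compliance-by-arm term, per SD of compliance, then estimates r_B − r_C instead of 0. Approximately,

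z = (r_B − r_C) / √[(2 − r_B² − r_C²) / (n − 3)], with critical value 1.993 (72 degrees of freedom).

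- 0.4 vs 0.1: 0.3 / √(1.83/35) = 0.3/0.229 = 1.31, so about 25% significant.
- 0.5 vs 0: 0.5 / √(1.75/35) = 0.5/0.224 = 2.24, so about 60%.
- 0.2 vs 0.1: 0.1 / √(1.95/35) = 0.1/0.236 = 0.42, so about 7%.

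Simulation of the least-squares model (arm, compliance, arm × compliance) agrees:

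| r_B vs r_C | Significant, r with the outcome itself | Significant, r with prognosis only |
|---|---|---|
| 0.3 vs 0.3 | 5% | 5% |
| 0.2 vs 0.1; 0.3 vs 0.2 | 6-8% | not run |
| 0.4 vs 0.1 | 26% | 18% |
| 0.5 vs 0.1 | 43% | 29% |
| 0.5 vs 0 | 59% | 41% |

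The last column is lower because the correlation is placed on prognosis and not directly on the outcome.

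**Step 2: bias when light does work.** Let the true effect be 0.8 SD at full compliance and proportional to compliance, with correlations 0.4 vs 0.1.

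- Interaction slope per unit of compliance: 0.8 + 0.3/0.20 = 2.3 (simulated 2.1-2.4).
- Effect at mean compliance: 0.8 × 0.75 = 0.60, which the model returns without bias.
- Effect at full compliance: 0.60 + 0.25 × 2.3 = 1.18, about 1.2 SD against a true 0.8. The bias is about 0.4 SD.
- Instrumental-variable ratio (difference between arms divided by mean compliance in the BLT arm): 0.60/0.75 = 0.80. Its SD over simulated trials is 0.31, against 0.40 for the naive estimate at full compliance. It recovers 0.80 because the simulation lets allocation act only through light.

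**Step 3: morning versus evening.** Assumptions: 35 BLT patients, compliance otherwise unconfounded, and only morning compliance has an effect (0.4 SD per SD). Evening compliance fitted alone then picks up 0.4 × ρ, where ρ is the morning-evening correlation.

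| ρ | Evening slope | Evening alone significant | Joint model: power for morning |
|---|---|---|---|
| 0.3 | 0.12 | 10% | 65% |
| 0.5 | 0.20 | 21% | 55% |
| 0.7 | 0.28 | 39% | 40% |
| 0.8 | 0.32 | 48% | 31% |
| 0.9 | 0.36 | 58% | 19% |

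The joint model keeps evening near 5%, but only because confounding was left out of this simulation.

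**The case against.** The article names no model for this analysis, gives it no confirmatory role and does not list compliance as an outcome. Model detail belongs in a full protocol or SAP that is not shown, and the inflation depends on correlations that the documents do not supply. With equal or nearly equal selection the interaction keeps roughly its nominal level. All of that stands, and it is why the size is given as a range. It does not remove the point. The stated aim itself asks a non-randomised exposure to explain the treatment effect, and no choice of regression model changes that.

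The objection also holds against any remedy that relies on instrumental variables alone. Such an estimate rescales the randomised difference and cannot say whether compliance modifies the effect. It needs a control lamp with no effect, and allocation acting only through light. The Discussion does not rule out an influence of 200 lux, and accepts that patients may recognise the dim lamp and that expectancy may affect outcome.

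A reader might infer four stronger things that the documents do not support:

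- That the protocol intends to claim that one session works and the other does not. It makes no such claim and leaves timing to further research.
- That the naive analysis turns 0.8 SD into more than 2 SD. That figure is the interaction slope. The like-for-like estimate at full compliance is about 1.2.
- That the false-positive rates of 20-68% found for a compliance slope within the BLT arm (correlations 0.2-0.4) apply here. The stated aim concerns the intervention effect, which involves both arms.
- That the primary result is compromised. It does not depend on this analysis.

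**Conclusion.** The point holds as a caution on a supporting analysis. Compliance is self-selected after randomisation. A compliance-by-arm term is safe under the null only if selection is alike in both arms, and the protocol article gives grounds to doubt that. Under assumed correlations, the chance of a false dose effect is 5% with equal selection, about 6-8% with small differences and about 18-59% with large ones. With a true effect of 0.8 SD and correlations of 0.4 vs 0.1, the effect at full compliance is overstated by about 0.4 SD. Separate morning and evening effects are not identified by randomisation, because both sessions are assigned to everyone at linked times. A joint model can produce two coefficients, but their causal reading needs unconfounded compliance, and power for the true one falls from 65% to 19% as the sessions become more correlated. The randomised comparison of HDRS change at T2 stands. A treatment coefficient adjusted for compliance would not have the same standing, because it conditions on behaviour that the assigned lamp may itself influence.

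**What to change.** Change the analysis wording as follows:

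1. Report compliance (total, morning, evening) descriptively by arm.
2. Label any association between compliance and outcome as exploratory and non-causal.
3. State that no conclusion on separate morning and evening effects will be drawn.
4. Remove compliance from the covariates tested by the 10% change-in-coefficient rule, so that it is never an adjustment variable for the treatment effect.
5. If an effect of light received is wanted, add a supporting two-stage least-squares estimate. The instrument is assigned arm, the dose is logged bright-light exposure in the BLT arm and 0 in the control arm, and the outcome is T2 HDRS adjusted for baseline. State beside it that it assumes no effect of the 200 lux lamp and no route from allocation to outcome other than light, and that the Discussion leaves both in doubt.

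No new data are needed. The cost is that the plan gives up a dose-response or session-specific reading. The instrumental-variable estimate does not replace it, since it only rescales the randomised difference under those assumptions. Loss of precision is not the main cost, because in the simulation this estimate varied less than the naive one.

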#### Side effects and treatment satisfaction

Prior to the start of the trial, we made an overview of potential adverse effects that subjects might experience during treatment, based on previous reports [41, 64]. One week after the start of treatment, subjects are contacted by telephone by the research assistant to inquire about these side effects. At assessment visit T1, patients are also screened for side effects. We will report the difference in prevalence of reported side effects between both groups.

After completing the treatment phase, all patients are asked to rate their appreciation of timing and duration of therapy sessions on a visual analogue scale (VAS). Moreover, they indicate on a VAS the extent to which they would like to continue treatment after the end of the trial. We will report average VAS scores as an indicator of treatment satisfaction per group.

### Statistical analysis

#### Sample size calculation

Prior to the start of the study, we calculated the necessary sample size for a sufficient power at the end of treatment (T2) in a mixed models analysis. We aimed to have sufficient sensitivity for a minimal standardized effect size of Cohen’s d = 0.6, with an estimated standard deviation of 1.0 and intra-subject correlation of assessments of *ρ* = 0.6. For a statistical power of 80 % and a two-tailed significance level of *p* < 0.05, 35 subjects per treatment group were required. To correct for a maximum drop-out of 20 %, we would need 7 additional subjects per group, resulting in a total sample size of 84 subjects.

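### The drop-out allowance is 35 × 1.2 rather than 35 / 0.8, so 84 patients do not keep 35 per group at the stated 20% drop-out

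*Protocol article*

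**What the plan says.** All inputs are in the section Sample size calculation of the protocol article. The trial is sized for the end of treatment (T2) under a mixed models analysis. The target is a "minimal standardized effect size of Cohen’s d = 0.6", "with an estimated standard deviation of 1.0", and an "intra-subject correlation of assessments of" ρ = 0.6. Power is set at 80% and the test is two-tailed at 0.05. From these the article concludes that "35 subjects per treatment group were required".

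The drop-out step follows directly. It opens with "To correct for a maximum drop-out of 20"% and ends with "we would need 7 additional subjects per group, resulting in a total sample size of 84 subjects". The article gives no other basis for the allowance. The Abstract repeats the total of 84.

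The section Efficacy analysis bears on what a drop-out costs. The modified intent-to-treat population keeps anyone who had at least a week of light treatment and at least one HDRS after baseline. Missing values are not imputed, and the mixed model uses whatever visits are available.

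**The concern.** The 7 extra subjects are 20% of 35. Drop-out, however, is lost from the patients enrolled, so the allowance has to be worked out on the enrolled number. Adding 20% and then losing 20% does not return to the starting figure.

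The article presents three numbers as holding together: 84 patients, up to 20% drop-out and 80% power. If the first two do not leave 35 per group, the third lacks the support claimed for it. The justification printed for the headline sample size is at stake. No part of the design or analysis turns on it.

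**Working it through.** **Inputs** (all from Sample size calculation): d = 0.6, SD = 1.0, ρ = 0.6, two-sided α = 0.05, power 80%, 35 per group required, drop-out at most 20%, 7 added per group, 84 in total.

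**Step 1: reproduce the 35.** For two means with variance factor f, n per group = 2 f (z₀.₉₇₅ + z₀.₈₀)² / d².

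- With f = 1 (correlation ignored): 2 × (1.96 + 0.8416)² / 0.36 = 43.6, so 44. This is not the article's figure.
- With f = 0.8: 43.6 × 0.8 = 34.88, so 35. This is the article's figure.

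The article does not state f. The value 0.8 is inferred because it returns 35. At ρ = 0.6 it arises in two ways: 2(1 − ρ) = 0.8 for a change score, and (1 + ρ)/2 = 0.8 for the mean of two assessments. The figures cannot tell these apart.

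**Step 2: reproduce the 84.** 35 × 0.20 = 7; 35 + 7 = 42; 2 × 42 = 84. The total comes from multiplying by 1.2.

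**Step 3: apply the stated drop-out to the enrolled number.** This step needs only the 35, the 7 and the 20%, and no variance factor.

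| Enrolled per group | Total | Left after 20% drop-out, per group |
|---|---|---|
| 42 | 84 | 42 × 0.8 = 33.6 |
| 43 | 86 | 43 × 0.8 = 34.4 |
| 44 | 88 | 44 × 0.8 = 35.2 |

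The number needed to keep 35 is 35 / (1 − 0.20) = 43.75, so 44 per group and 88 in total, 4 more than planned. The largest drop-out that 42 per group can absorb is (42 − 35)/42 = 7/42 = 16.7%.

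**Step 4: the cost in power.** On the normal approximation, power = Φ( d / √(2f/n) − 1.96 ) with f = 0.8. Drop-outs are assumed to contribute nothing.

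| n per group at T2 | Power |
|---|---|
| 35 | 80.1% |
| 34 | 79.0% |
| 33.6 | 78.5% |
| 33 | 77.8% |

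For example, at n = 33.6, √(1.6/33.6) = 0.2182; 0.6/0.2182 = 2.75; 2.75 − 1.96 = 0.79; Φ(0.79) is about 0.785. The loss at 20% drop-out is 80.1 − 78.5 = 1.6 percentage points.

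**The case against.** **Drop-outs are not all lost.** This is the strongest argument on the other side, and part of it stands. The planned model keeps a patient who has a T1 HDRS but no T2. How much that recovers depends on what is tested. Suppose the calculation rests on the mean of two visits with a common effect. A T1-only patient then has variance 1 against 0.8 for a full patient, and so carries 0.8 of the information. The 1.4 per group that are missing (35 − 33.6) would be restored by 1.4/0.8 = 1.75, about 2 of the 8.4 drop-outs per group. For a baseline-adjusted contrast at T2 alone, with equal correlations, recovery is slight: about 34.6 effective patients per group even if every drop-out has a T1 value. The 1.6 points are therefore an upper limit on this approximation. The argument does not rescue the printed step, which adds patients to make up for drop-out from a required 35 and takes no credit for partial data.

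**The shortfall is trivial.** It is 1.4 patients per group and appears only when drop-out exceeds 16.7%, with 20% described as a maximum. That is a fair reason to rank the point low. The stated combination is still arithmetically wrong, and condensing a protocol into an article does not explain it, because this is a printed figure and not an omission.

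**Stronger readings that the document does not support.**

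- A reader might infer that the 35 is a change-score calculation, and so conflicts with the baseline-corrected analysis under Efficacy analysis. The article names no such formula, and 0.8 fits a mean of two assessments equally well.
- A reader might go further and say that only 28 per group are needed, using 1 − 0.6² = 0.64 and 43.6 × 0.64 = 27.9. That takes ρ = 0.6 to be the baseline-to-T2 correlation, which the article does not say. It also reduces the planned mixed model to a simple baseline-adjusted comparison at T2.
- A reader might set a t-based power of 77.3% at 33.6 per group against the 80% target. By the t distribution, 35 per group already gives only 79.0%, so the like-for-like loss is 79.0 − 77.3 = 1.7 points, much the same as before.

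**Conclusion.** The drop-out allowance is wrong as written. At the stated maximum of 20%, 84 patients leave 33.6 per group instead of 35. The planned number covers drop-out up to 16.7%, and a full 20% allowance would take 88. This rests only on figures printed in the article.

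The consequence is minor: at most about 1.6 points of power, from 80.1% to about 78.5%. That size depends on the normal approximation, on the inferred variance factor of 0.8, and on drop-outs contributing no information. With partial data in the mixed model the loss is smaller. The finding does not show that the trial is materially underpowered, nor that the sample size rests on a different analysis from the one planned.

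**What to change.** Keep 84 and correct the drop-out statement in Sample size calculation. Suggested text: *With 42 patients per group (84 in total), 35 per group are retained for drop-out up to 16.7%. At 20% drop-out about 33 to 34 per group remain, giving about 78 to 79% power on the calculation that yielded 35, if patients who drop out contribute no information.*

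The cost is two sentences and a slightly less favourable stated power. No additional patients are needed and the analysis does not change. If the sponsor wants to keep the claim of 35 per group at 20% drop-out, the total has to read 88, which is 4 more patients.
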